## Abstract

**Background:**

Obesity is an increasing disease worldwide. Bariatric surgery is the only effective therapy to induce sufficient long-term weight loss for morbidly obese patients. Laparoscopic Roux-en-Y Gastric Bypass (LRYGB) is the gold standard surgical technique. Laparoscopic Sleeve Gastrectomy (LSG) is a new promising bariatric procedure which has the advantage of maintaining an intact gastrointestinal tract. The aim of this study is to evaluate the efficiency of both techniques. Our hypothesis is that LSG has a similar percentage excess BMI loss (%EBMIL) after 5 years compared to LRYGB.

**Methods/Design:**

The Sleeve Bypass Trial is a randomized multicentre clinical trial: patients eligible for bariatric surgery are randomized to either LSG or LRYGB. Patients with a body mass index (BMI) ≥ 40 kg/m^2^ or BMI 35 kg/m^2^ with obesity related comorbidity (T2 DM, sleep apnoea, hypertension) are eligible for randomization. At randomization patients are stratified for centre, sex, T2 DM and BMI ≥ 50 kg/m^2^. A total number of 620 patients will be enrolled and equally (1:1) randomized to both treatment arms. Only surgeons experienced in both operation techniques will participate in the Sleeve Bypass trial. The primary endpoint is the 5-year weight loss (%EBMIL) of LSG and LRYGB. Secondary endpoints are resolution of obesity related comorbidity, complications, revision bariatric surgery and quality of life (QOL) defined in various questionnaires.

**Discussion:**

Long-term %EBMIL between the two treatment strategies used to be in favour of LRYGB, but more recent results throughout the world show similar %EBMIL in both techniques. If weight loss is comparable, obesity-related comorbidity and QOL after bariatric procedures should be taken into account when deciding on which surgical technique is to be preferred for certain subgroups in the future.

**Trial registration:**

Dutch Trial Register: NTR 4741.

## Background

Obesity is a global problem. It induces health risks, diminishes quality of life, psychosocial problems and increases public costs. When patients become morbidly obese, health risks increase rapidly [1]. Morbid obesity is defined as having a body mass index (BMI) ≥ 40 or BMI 35 kg/m^2^ combined with at least one comorbid condition, such as type 2 diabetes (T2 DM), hypertension, dyslipidaemia, or sleep apnoea.

Bariatric surgery is considered the best treatment to realize long-term sufficient weight loss in morbidly obese patients [2–4]. Besides weight loss, it also has profound effects on obesity-related comorbidities, such as T2DM, hypertension and sleep apnoea [5, 6].

Laparoscopic Roux-en-Y gastric bypass (LRYGB) is considered the best surgical option for morbid obesity and as a result is still one of the most frequently performed bariatric procedure worldwide [7, 8]. There are advantages of LRYGB being fully reversible, well documented in terms of early morbidity and long term results known for more than 50 years and often regarded as the gold standard in bariatric and metabolic surgery. Laparoscopic sleeve gastrectomy (LSG) is a relatively new procedure which started as a first stage procedure before a duodenal switch (DS) in super obese patients to reduce treatment related mortality. As weight loss results following LSG were excellent, necessitating a second stage procedure in only a quarter of the patients, LSG is currently used as a single stage procedure in morbidly obese patients. LSG is becoming more popular and is performed in 28 % of bariatric procedures worldwide in 2011 [8]. LSG has some potential advantages; it is a faster and safe procedure where the duodenum is still accessible for endoscopy, there is less dumping due to the pylorus and second stage procedures (LRYGB or BPD-duodenal switch) are standard procedures. The most profound possible disadvantage is that LSG is irreversible. Quality of life (QOL) appears to be similar or even better after LSG compared to LRYGB due to the mentioned advantages [9, 10].

So far results of RCTs with small number of patients and short-term outcome have been published only. In these studies the percentage excess BMI loss (%EBMIL) appeared to be equal for both techniques [9, 11–16]. However, concerns remain that the sleeve will lose its effect in time, resulting in a decline of weight loss and reappearance of obesity-related comorbidity [17].

## Methods/Design

### Study objective

The primary aim of this multicentre study is to compare LSG with standard LRYGB in terms of percentage excess BMI loss (%EBMIL) as well as in secondary outcomes (e.g. QOL, resolution of obesity-related-comorbidity, complications and revision bariatric surgery due to insufficient weight loss or GERD). In order to determine the area of indication for the LSG in the field of bariatric surgery patients in this study are also stratified at randomisation for sex, T2 DM and a BMI below or above 50 kg/m^2^.

### Study design

The sleeve versus bypass trial is a randomized multi-centre trial, in which two bariatric medical centres are participating. The study started on November 24th 2012 and the duration of the inclusion will be approximately 3 years. The study compares the %EBMIL of LSG and LRYGB after five years (primary endpoint). Patients with morbid obesity with a BMI ≥ 40 kg/m2 or BMI 35 kg/m2 with obesity related comorbidity (T2 DM, sleep apnoea, hypertension) are eligible for randomization. In total 620 morbidly obese patients will be included in the study. Approval of the medical ethical committee of both participating centres, “Toetsingcommissie Wetenschappelijk Onderzoek Rotterdam” and “Medisch Ethische Toetsingcommissie Catharina Ziekenhuis Eindhoven” was obtained. After approval the trial is accepted and registered in the Dutch trial register. The complete route of patient inclusion and randomisation is depicted in Fig. 1.

**Fig. 1 Fig1:**
[figure not shown]
CONSORT flowchart

Patients will be randomized, using a randomization website to one of the following bariatric procedures:Laparoscopic sleeve gastrectomy (LSG)The LSG is performed by a full mobilisation of the greater curvature and the posterior stomach, followed by stapling calibrated over a 34 french boogie, starting 2–3 cm’s from the pylorus. The used technique is described in 2012 and proven to be effective and safe [18].Laparoscopic Roux-and-Y gastric bypass (LRYGB)The LRYGB is performed with the antecolic linear technique. A small 4 cm long pouch is calibrated over a 34 french boogie and 3 cm linear gastroenterostomy is realized. The measured biliopancreatic limb is 60 cm and the alimentary limb is 150 cm. The omentum can be divided at the surgeons’ discretion. Both mesenteric defects are closed with clips [19].

### Patient selection

All morbidly obese patients who have been approved for bariatric surgery by the preoperative multidisciplinary team can be included in the sleeve versus bypass trial. Informed consent is mandatory. The criteria for bariatric surgery are age 18–60 years, BMI > 40 kg/m^2^, or BMI > 35 kg/m^2^ with obesity-related comorbidity (such as T2 DM, hypertension, hypercholesterolemia, severe arthrosis and OSAS) for more than 3 years, conservative therapy (preferably under the guidance of a physician or self-help group) that has failed or showed only transient results, completion of psychological screening, excluding patients with psychiatric and psychological disorders, written informed consent and willingness to conclude the lifelong follow up program after surgery.

Exclusion criteria for this study are: a history of diagnosed symptomatic gastro oesophageal reflux disease (GERD) [20], or a diagnosed hiatal hernia with symptoms. There is no routine gastroscopy prior to surgery in asymptomatic patients. Other exclusion criteria are severe sweet eating [21], prior bariatric surgery, prior major abdominal surgery (such as colonic resection, abdominal sepsis, aortic surgery, which might jeopardise the technical feasibility of LSG or LRYGB) and the inability of reading or understanding the questionnaires.

### Hypothesis

Our hypothesis is that LSG has a comparable %EBMIL after 5 years when compared to LRYGB [22–26]. Even if LSG is marginally less effective compared to LRYGB in terms of long term %EBMIL, QOL might be better from a dietary and long term complications point of view [27-29].

### Study questions

Primary Question: Does LSG result in a similar long term %EBMIL after a follow up period of 5 years when compared to the LRYGB?

Secondary Question: Is the QOL better after a LSG compared with the LRYGB?

Other secondary endpoints: improvement in obesity induced co-morbidity, complication rate, readmission and reoperation rate, revision surgery rate, operating time and duration of hospital stay and the predictive value of sweet eating habit inventoried by the Dutch Sweet Eating Questionnaire (DSEQ) [21].

### Surgical intervention

All patients are treated in a fast-track protocol [30] and discharged 1 day after surgery. Antithrombotic prophylaxes (Fragmin® 5000 u/day) and a fluid diet is continued for 2 weeks postoperatively. All patients are prescribed proton pump inhibitors for 6 weeks after surgery. Follow up of patients will be performed in an outpatient clinical setting [Table 1].

**Table 1 Tab1:** Follow up after surgery

Follow up	History/Examination	Weight/Complications	Questionnaires^a^
1 Week	Obesity nurse	Obesity nurse	
6 Weeks	Surgeon	Surgeon	Obesity nurse
3 Months	Endocrinologist^b^	Endocrinologist^b^	
6 Months	Endocrinologist^b^	Endocrinologist^b^	Obesity nurse
9 Months	Endocrinologist^b^	Endocrinologist^b^	
12 Months	Surgeon	Surgeon	Obesity nurse
Annualy	Endocrinologist^b^	Endocrinologist^b^	Obesity nurse

^a^Changes in health status over time are measured using generic and disease specific quality of life questionnaires (Euro-Qol 5D, Short Form 36 (SF-36) and the Gastro-Intestinal Quality of Life Index (Qiqli)) on admission and after 6, 12 months and then annually. Obesity related quality of life questionnaires (the Moorehead-Ardelt II) and the Bariatric Analysis and Reporting Outcome System (BAROS) score are measured at the same time-intervals. Sweet eating will be established with the Dutch Sweet Eating Questionnaire (DSEQ)

^b^Every visit to the endocrinologist is combined with extensive laboratory testing

The patient is called by the obesity nurse in the first week. Outpatient clinic visits are scheduled at 6 weeks, 3, 6 and 12 months and then once annually. The standard follow up [Table 1] is combined with extra visits in case of complaints or possible complications with a 24 h access to the bariatric surgery department. The complications are scored at every consultation using the “Clavien-Dindo classification” to score the severity [31].

All participating surgeons are experienced bariatric surgeons that have performed at least 150 LSG and 150 LRYGB and work in bariatric centres of excellence that perform over 500 cases per year.

#### Laparoscopic sleeve gastrectomy

Two different known approaches have been described in the literature [32, 33]: the stapling first technique or the full mobilisation of the greater gastric curvature first technique. As a tight gastric sleeve, which is important for an optimal weight loss result, seems to be realised best by the gastric mobilisation first technique [18] this is the only LSG technique used for this study.StartingAfter achieving pneumoperitoneum, with a Veress needle in the left upper quadrant, five trocars are placed according to the surgeons preference.MobilizationThe greater curvature is dissected downward to 2–3 cm proximal to the pylorus. Next the greater curve is further mobilized up to the angle of His, visualizing the complete left diaphragm crus. While mobilizing the greater curve all gastro-pancreatic adhesions at the dorsal smaller gastric curve are also released in upward direction towards the angle of His. This step is important in order to be able to realize a small gastric sleeve without redundant fundus at the dorsal gastric wall.StaplingA linear 60 mm endoscopic stapler is introduced through the right trocar and fired at the antrum, leaving just enough space for a gastric boogie to pass. Next an orally introduced gastric tube is inserted up to the pylorus. This gastric tube is 34 French (Fr) in diameter as it is important to create a small gastric sleeve. A tight sleeve is realised by firing another 4–5 60 mm long linear staple lines using the same trocar site. The stapler is placed tight to the tube while stretching the greater curve. Each time after placing the stapler the gastric tube is moved by the anaesthesiologist under laparoscopic vision in order to ensure that the stapler has not been placed on the tube itself. The last stapler is fired lateral to Belsy’s fat leaving the oesophagus unharmed.FinishingNext, the left trocar site is dilated and the resected stomach is removed. Subsequently, this trocar site is closed at fascia level. The gastric tube is removed by the anaesthesiologist under laparoscopic vision. Staple line bleeding is controlled by clips and when necessary with sutures. Only in case of bleeding, stapling problems, or other difficulty, a drain is placed along the sleeve gastrectomy. Over-sewing of the staple line is not routinely performed. Next, the trocars are removed under sight and the skin is closed.

#### Laparoscopic Roux-en-Y gastric bypass

StartingAfter achieving pneumoperitoneum, with a Veress needle in the left upper quadrant, five trocars are placed according to the surgeons preference.Gastric pouch creationAt the gastro oesophageal junction Belsy’s fat is released from the left diaphragm crus.Next, at the lesser curve, approximately 4 cm below the angle of His, the minor omentum is released from the lesser gastric curve until an opening is created in the omental burse. A 60 mm linear endostapler is used to transect the lesser curve horizontally. Then, the gastro-pancreatic adhesions are released and 2 more 60 mm linear endostaplers are fired in vertical direction along a calibrating 34 Fr gastric tube that has been inserted transorally. Thus a small and calibrated gastric pouch is created.Omental splitIn order to make the pathway of the small bowel towards the gastric pouch shorter the greater omentum can be split vertically.Creation of gastro-enterostomyThe small bowel is brought upward towards the gastric pouch at a length of 60 cm from the point of Treitz. At this point a small defect is created in the small bowel as well as in the left caudal corner of the pouch. A linear endostapler is fired at 3 cm’s length. The anastomosis is closed by laparoscopic suturing. The gastro-enterostomy is tested by methylene blue injected through a gastric tube. If the test indicates leakage, this point is sutured and the methylene blue test is repeated.Creation of entero-enterostomyA linear stapler is fired and the remaining defect is sutured creating an entero-enterostomy between the small bowel proximal to the gastro-enterostomy and the small bowel 150 cm distally from the gastro-enterostomy.FinishingPetersen’s space and the mesenteric defect at the entero-enterostomy are closed by a laparoscopic clipping device [19]. Staple line bleeding is controlled by clips and when necessary with sutures. The trocars are removed under sight and the skin is closed.

#### Escape surgery

If it is technically impossible to perform an LRYGB during surgery, it is allowed to perform a LSG. Moreover, if there are technical problems during LSG e.g. creating an occlusion of the sleeve or stapling of the oral tube, conversion to LRYGB surgery is allowed. The statistical analysis will be according to the intention-to-treat principle and a per protocol analysis.

### Outcome measures

#### Primary endpoint

Sustainable weight loss. The amount of weight loss is expressed as percentage excess BMI loss (%EBMIL), and calculated with the formula %EBMIL = (pre-operative BMI – current BMI)/(pre-operative BMI – ideal BMI) × 100 %. For this formula a BMI of 25 kg/m^2^ was taken as the upper limit of normal, i.e. the ideal BMI.

#### Secondary endpoints

To evaluate operating time, duration of hospital stay, intra-operative and post-operative in-hospital mortality and morbidity following LSG or LRYGB. Morbidity is defined as re-operations, re-interventions, re-admissions and serious adverse events. Morbidity is also defined as major (anastomotic leakage, major peroperative blood loss due to splenic or vascular haemorrhage, pulmonary embolism, intra-abdominal abscess and intra-abdominal hematoma) or minor (wound infection, urinary tract infection and anastomotic stenosis). Moreover, the rate of extra outpatient and emergency room visits because of complaints following LSG or LRYGB are evaluated.

Preoperatively all patients are assessed by an multidisciplinary team consisting of at least surgeons, endocrinologists, physiotherapists, nutritionists, and psychiatrists.

The endocrinologist defines the comorbidities using the definitions from common international guidelines [34] for hypertension, dyslipidaemia, T2 DM, obstructive sleep apnoea syndrome (OSAS) and joint pain. The surgeon defines gastro oesophageal reflux disease (GERD) as need for proton pump inhibitor (PPI) agents and/or esophagitis diagnosed on endoscopy. To evaluate the biochemical changes following LRYGB or LSG in the first year extensive laboratory tests are obtained every 3 months. This is continued in the yearly visits which are common practice in our clinics. If patients fail to attend follow up they will be contacted by telephone to motivate them to return to the follow up or the patient’s general practitioner will be contacted in order to minimize the lost-to-follow up. To evaluate remission or improvements of the various comorbidities the use of medication is documented and adjusted where necessary during each visit. The remission of a co-morbidity was defined when patients no longer needed a drug therapy and had normal blood pressure. In T2 DM remission was defined as a normal fasting glucose, without medication and a glycosylated haemoglobin (HbA1c) of <6 %. Improvement was defined as changing from insulin to oral antidiabetic drugs or lowering the dose or number of drugs needed.

To evaluate QOL multiple questionnaires are used. QOL was objectified by the asthma control questionnaire (ACQ), the reflux disease questionnaire (Gerd-Q), the Bariatric Analysis and Reporting Outcome System (BAROS) score, the Gastro-intestinal Quality of life Index (GIQLI), EuroQol-5D (EQ-5D), Short-form 36 (SF-36) before and following LSG or LRYGB.

To evaluate the predictive value of the Sweet eating inventoried by the Dutch Sweet Eating Questionnaire (DSEQ) [17].

To evaluate the need for revision surgery (need to perform an additional bariatric procedure after the performed surgery) as a result of insufficient weight loss or medical complaints within 5 years following the primary bariatric procedure (LSG or LRYGB). Insufficient weight loss is defined with the Reinhold criteria (modified by Christou and Biron).

All data will be collected in a digital patient form in order to ensure completeness of data.

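### The major/minor morbidity list names leakage and stenosis only as anastomotic, so read literally it leaves out a sleeve staple-line leak and a sleeve stenosis

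*Protocol article*

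**What the plan says.** The protocol article describes morbidity in three ways.

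- Secondary endpoints first gives a definition that does not depend on the operation: "Morbidity is defined as re-operations, re-interventions, re-admissions and serious adverse events".
- The next sentence adds a split by named events: "Morbidity is also defined as major (anastomotic leakage, major peroperative blood loss due to splenic or vascular haemorrhage", continuing with "pulmonary embolism, intra-abdominal abscess and intra-abdominal hematoma"; and "minor (wound infection, urinary tract infection and anastomotic stenosis". Both lists stand in parentheses with nothing to mark them as examples.
- Surgical intervention adds a severity scale for both arms: "The complications are scored at every consultation using the" Clavien-Dindo classification.

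The section on laparoscopic sleeve gastrectomy describes a gastric staple line and no anastomosis, and says of it: "Over-sewing of the staple line is not routinely performed". The section on laparoscopic Roux-en-Y gastric bypass describes a gastro-enterostomy and an entero-enterostomy. Escape surgery gives, as examples of technical problems during LSG that allow conversion, "creating an occlusion of the sleeve or stapling of the oral tube". Complication rate is a secondary endpoint under Study questions.

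**The concern.** In a comparison of two operations, an event definition should not depend on which operation was done. Here the only leak item and the only stenosis item are tied to a structure that one operation creates and the other does not. The abstract makes the contrast itself, saying that LSG "has the advantage of maintaining an intact gastrointestinal tract". A coder who follows the list word for word would enter a leak at the gastro-enterostomy as major morbidity and would have no line for a leak from the sleeve's staple line. Stenosis behaves the same way on the minor list.

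Such an error is differential. It goes in one direction, and more patients do not average it out. The direction matters because the Hypothesis section argues that LSG might offer a better quality of life from a dietary and complications standpoint even if it is marginally less effective on weight. A major/minor table that undercounts LSG events would support that argument for a reason that has nothing to do with the patients.

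**Working it through.** **Step 1. Items side by side.**

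| Item | List | LRYGB as described | LSG as described |
|---|---|---|---|
| Anastomotic leakage | major | possible at two anastomoses | no anastomosis; staple-line leak not named |
| Anastomotic stenosis | minor | possible | no anastomosis; sleeve stenosis not named |
| Major blood loss, pulmonary embolism, abscess, haematoma | major | possible | possible |
| Wound infection, urinary tract infection | minor | possible | possible |

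Two items are worded for one operation. The rest apply to both.

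**Step 2. Denominator.** The document has no figure for complications. The only stated figure needed is the number per arm (Power calculation), and it reproduces. With a difference of 68.59 − 62.60 = 5.99, SD 25.88, two-sided alpha 0.05 and power 80 %:

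n = 2 × (1.960 + 0.842)² × 25.88² / 5.99² ≈ 293.03, rounded up to 294 per arm; 294 / 0.95 = 309.5, rounded up to 310; 2 × 310 = 620.

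It rests on %EBMIL alone, so nothing here changes it.

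**Step 3. Size of the gap, under assumptions.** Let L be the true rate of leak plus stenosis, equal in both arms, and s the share of LSG events that go uncounted. The artificial gap is L × s, or 310 × L × s events. L of 1–3 % is assumed. All LRYGB events are taken to be anastomotic, and there are no conversions.

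| L | s = 0 | s = 0.5 | s = 1 |
|---|---|---|---|
| 1 % | 0 | 0.5 points (1.55 events) | 1 point (3.1 events) |
| 2 % | 0 | 1.0 point (3.1 events) | 2 points (6.2 events) |
| 3 % | 0 | 1.5 points (4.65 events) | 3 points (9.3 events) |

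Leak belongs to the major row and stenosis to the minor row, so this is the gap for the two rows together. On either row alone it cannot exceed that row's own rate.

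**Step 4. What a test would make of it (illustration only).** Add other listed events at an assumed 3–5 % in each arm and compare the arms with a two-sided 5 % test of proportions. The probability of a result in favour of LSG is Φ[(d − 1.96 × SE₀) / SE₁], where d is the gap, SE₀ the pooled and SE₁ the unpooled standard error. For 6 % against 3 %: SE₀ = √(2 × 0.045 × 0.955 / 310) = 0.01665, SE₁ = √((0.06 × 0.94 + 0.03 × 0.97) / 310) = 0.01661, giving Φ(−0.159) = 0.44. For 6 % against 5 % the result is 0.08. Across the assumed range it is about 8–44 % if every LSG leak and stenosis is missed and about 5–13 % if half are, against 2.5 % in that direction when none is missed. The article specifies no such test for the major/minor table, so these figures show scale only.

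**The case against.** The strongest reply is that the event is captured elsewhere. The sentence just before the list defines morbidity neutrally, so a sleeve leak or stenosis that leads to re-operation, re-intervention, re-admission or a serious adverse event counts in the LSG arm. Clavien-Dindo grading covers both arms, and physicians must report potential adverse events to the monitoring committee. Study questions names complication, readmission and reoperation rates without tying them to the major/minor list. All of this stands. A reader might infer that the whole complication comparison is biased towards LSG; the document does not support that.

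Nor is the asymmetry all-or-none. A leak may present as an intra-abdominal abscess, which is listed for both arms. The bypass pouch has staple lines of its own, and a leak there would also fall off a literal list. Under intention to treat, an LSG patient converted to LRYGB can have an anastomotic event in the LSG arm, and a bypass patient converted to LSG has no anastomosis. These points narrow the gap but do not close it.

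A reader might also infer that limiting major blood loss to splenic or vascular sources hides sleeve staple-line bleeding. That shows no tilt: the sections on both operations describe control of staple-line bleeding in the same terms, and intra-abdominal haematoma is major in either arm. It is equally tempting to assume a leak rate, score every bypass leak and no sleeve leak, and test the leak row alone. Any significance would come from the assumed rate and from assuming complete non-capture, and the document supplies neither.

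Finally, this is a condensed article, and fuller event definitions may stand in the full protocol or case report form. But this is not a case of missing detail: the article states the list, and states it in terms of one operation. The neutral definition does not repair it either, because the split is introduced as an additional definition and no rule links it to the Clavien-Dindo grade.

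**Conclusion.** The point holds for the major/minor classification only. Taken literally, the list undercounts staple-line leaks and sleeve stenoses, and any resulting distortion favours LSG. Its size cannot be computed from the document. With equal true leak-plus-stenosis rates of 1–3 % per arm, it runs from zero, if coders treat a staple-line leak and a sleeve stenosis as the listed events, to about 3 percentage points (about 9 of 310 patients), if none is counted. The upper end assumes the highest rate, complete non-capture, no conversions and no bypass leaks outside the anastomoses, so it is an outer bound within the assumed range. The procedure-neutral morbidity definition, the Clavien-Dindo grades, the primary endpoint and the sample size are untouched. Severity: should-fix.

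**What to change.** In Secondary endpoints, change the leak item to *anastomotic or staple-line leakage* and the stenosis item to *anastomotic or sleeve stenosis*, and state that both apply identically in the two arms. The revised leak item also brings in leaks from the bypass pouch staple line. Report the between-arm severity comparison on the Clavien-Dindo grades as well, so that the major/minor table does not stand alone.

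The cost is a change to two items in an endpoint definition. The grades are already recorded at every consultation, and no visit, patient or sample-size change is needed. Events already coded under the literal wording should be checked once against the revised items, in both arms and in the same way.

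### As written, remission of dyslipidaemia, sleep apnoea and joint pain requires a normal blood pressure and no measure of the condition itself

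*Protocol article*

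**What the plan says.** All of the following is in the Protocol article, mostly under Outcome measures, Secondary endpoints.

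- The endocrinologist applies guideline definitions (reference 34) "for hypertension, dyslipidaemia, T2 DM, obstructive sleep apnoea syndrome (OSAS) and joint pain". GERD is defined separately, by the surgeon.
- Follow-up information on these conditions is introduced in general terms: "To evaluate remission or improvements of the various comorbidities the use of medication is documented and adjusted where necessary during each visit".
- The next sentence is the remission rule: "The remission of a co-morbidity was defined when patients no longer needed a drug therapy and had normal blood pressure".
- One exception follows: "In T2 DM remission was defined as a normal fasting glucose, without medication and a glycosylated haemoglobin (HbA1c) of <6" per cent.
- Improvement is then defined by drugs only: "Improvement was defined as changing from insulin to oral antidiabetic drugs or lowering the dose or number of drugs needed".

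The Abstract (Methods/Design) gives the endpoint its standing: "Secondary endpoints are resolution of obesity related comorbidity, complications, revision bariatric surgery and quality of life (QOL) defined in various questionnaires". The Abstract's Discussion adds that, if the two operations give comparable weight loss, comorbidity and quality of life should inform the choice between them.

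**The concern.** The general rule has one physiological criterion, blood pressure. That suits hypertension. It does not measure dyslipidaemia, sleep apnoea or joint pain, yet the text applies it to a comorbidity in general and exempts only diabetes.

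Two things are at stake. First, patients can be put in the wrong category: someone whose lipids are normal without drugs fails the rule if blood pressure is raised. Second, the outcomes stop being separate. If blood pressure is a component of each, a difference between the arms in blood pressure alone would appear as a difference in lipid, sleep apnoea and joint-pain remission, or could hide a real one. The trial's hypothesis is that weight loss is comparable, which is the case in which the protocol wants comorbidity results to be weighed.

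**Working it through.** **Scope of the rule.** Set the passages side by side.

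| Condition listed | Remission rule that applies as written | Measure of the condition required? |
|---|---|---|
| Hypertension | No drug need + normal blood pressure | Yes |
| T2 DM | Own rule: fasting glucose, no medication, HbA1c | Yes |
| Dyslipidaemia | No drug need + normal blood pressure | No |
| Sleep apnoea | No drug need + normal blood pressure | No |
| Joint pain | No drug need + normal blood pressure | No |

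The preceding sentence concerns the various comorbidities, so nothing in the context limits the rule to hypertension. Reference 34 is attached to how the comorbidities are defined. The text does not say that it also defines remission.

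**The plan's own figure.** The only related figure is the sample size (Power calculation), and it reproduces. With a difference of 68.59 − 62.60 = 5.99, SD 25.88, two-sided alpha 0.05 and power 80 %, n = 2 × (1.960 + 0.842)² × 25.88² / 5.99² ≈ 293.0, rounded up to 294 per arm. Then 294 / 0.95 = 309.5, rounded up to 310 per arm, 620 in total. The remission rule does not enter this calculation.

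**Can the error be sized?** The document gives no remission rates and no blood-pressure rates. The figures below are assumptions, used only to see what could be concluded. Let p be the true remission of a non-hypertensive condition and q the share with normal blood pressure, independent of p. Two readings of the drug clause bracket the result.

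- Strict: a patient whose condition persists still needs a drug and so fails. Recorded remission = p × q.
- Loose: everyone meets the drug clause. Recorded remission = p × q + (1 − p) × q = q.

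| p | q | Strict: p × q | Loose: q |
|---|---|---|---|
| 60 % | 50 % | 30 % | 50 % |
| 60 % | 60 % | 36 % | 60 % |
| 60 % | 80 % | 48 % | 80 % |
| 40 % | 80 % | 32 % | 80 % |
| 80 % | 40 % | 32 % | 40 % |

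The strict reading can only understate remission. The loose reading can understate it (80 % recorded as 40 %), overstate it (40 % recorded as 80 %), or leave the total unchanged while misplacing individuals. At p = q = 60 %, 0.60 × 0.40 = 24 % of patients are wrongly not remitted and 0.40 × 0.60 = 24 % wrongly remitted.

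**Carry-over between arms.** Take the same true remission of 60 % in both arms, and normal blood pressure in 60 % of one arm and 80 % of the other. Recorded remission is 36 % against 48 % on the strict reading (12 points) and 60 % against 80 % on the loose one (20 points). The true difference is zero. The carry-over occurs on both readings; its size depends wholly on the assumed inputs.

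**The case against.** The best defence is a drafting slip. The sentence stands directly before the diabetes rule, and the pair reads naturally as a hypertension rule followed by a diabetes rule, with one word missing. The article condenses a fuller protocol that may hold criteria for the other conditions, and few investigators would apply blood pressure to joint pain. This is plausible, and it means that the absence of detailed criteria is not in itself a fault. It does not rescue the sentence, which states a rule for comorbidities in general and needs correcting on either view.

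Other parts of the defence stand and limit the point:

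- A reader might infer a definite bias, for instance that a true 60 % would be recorded as 30–48 %. That counts only wrongly withheld remission and rests on an unsourced 20–50 % with raised blood pressure. Once wrongly granted remission is allowed, the direction is open.
- A reader might infer that patients with sleep apnoea meet the drug clause from the start, so that blood pressure alone decides. The clause speaks of no longer needing drugs, which may presuppose earlier need. The document does not say how sleep apnoea is treated, so the rule may simply be inapplicable there.
- Likewise, a patient who stops lipid drugs with abnormal lipids may still need them, and so is not clearly counted as remitted.
- The endpoint is listed first among secondary endpoints only in the Abstract. Study questions makes quality of life the secondary question and places comorbidity among the others.
- GERD has its own definition, and diagnosed symptomatic GERD is an exclusion criterion, so it adds little here.

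**Conclusion.** The point holds as a wrongly stated endpoint definition. As written, normal blood pressure is required for remission of three conditions that it does not measure, and no measure of those conditions is required. The certain consequences are that a resolved condition with raised blood pressure counts as not remitted, and that an arm difference in blood pressure carries into the other outcomes. Both assume that the rule is applied as written.

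Neither the size nor the net direction of the error can be computed from the document. The damage is confined to a secondary endpoint. The remission rules for hypertension and type 2 diabetes are adequate, and a reader should not infer that the primary comparison of %EBMIL or the sample size is affected.

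**What to change.** - State that the blood-pressure criterion applies to hypertension only.
- Define dyslipidaemia remission as no lipid-lowering drugs and normal lipids at the scheduled laboratory test. Medication is recorded at every visit, and extensive laboratory tests are scheduled every three months in the first year and at the yearly visits.
- For sleep apnoea and joint pain, use a condition-specific criterion built on data the trial actually records. The article describes no follow-up sleep test, device-use record or dedicated joint-symptom instrument. If none exists, report only medication or treatment status and do not call it remission.
- Fix these definitions before the 5-year analysis, so that they are not chosen with results in view.

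The cost is a short definition table and a little programming. Visits, sample size and treatment stay the same. The real downside is that the trial may be unable to claim remission of sleep apnoea or joint pain.
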